**Appendix N**

**Lay Counselor Observation Form**

Instructions: To be completed while observing a lay counselor during an individual visit with a patient.

Observer ID #: __________

Lay counselor ID #: __________

Date of interview: ( ____ **/** _____ **/ ____**____)

dd mm yyyy

Assessment Number:

_____ 1. Baseline assessment

_____ 2. 6-month assessment

_____ 3. 12-month assessment

Patient session start time**:** __________

Patient session end time**:** __________

Total visit time**:** __________ minutes *[Calculate after visit is over]*

Circle the appropriate answer to each question below:

|  | **No** | **Yes** | ***Not applicable*** |
| --- | --- | --- | --- |
| 1. Is the HIV prevention poster on the wall in the office? | 0 | 1 | *-3* |
| 1. Is the HIV prevention poster on the wall in the waiting area? | 0 | 1 | *-3* |
| 1. Is the HIV prevention job aid in a place where it can be easily viewed and/or used? | 0 | 1 | *-3* |
| 1. Is the session taking place in a private location? | 0 | 1 | *-3* |

For each of the items below, circle whether the counselor discussed the topic with the patient. If provider did not discuss the topic, provide information why the provider did not discuss.

|  | **No** | **Yes** | ***Not applicable*** |
| --- | --- | --- | --- |
| 1. Discuss disclosure of HIV status to partner(s) | 0 | 1 | *-3* |
| 1. Discuss partner’s HIV status | 0 | 1 | *-3* |
| 1. Encourage patients to bring their partner(s) to the clinic for HIV testing. | 0 | 1 | *-3* |
| 1. Give patient partner HIV testing slips | 0 | 1 | *-3* |
| 1. Discuss safer sex behaviors | 0 | 1 | *-3* |
| 1. Discuss abstaining from sex | 0 | 1 | *-3* |
| 1. Discuss reducing number of sex partners | 0 | 1 | *-3* |
| 1. Discuss using condoms consistently and correctly | 0 | 1 | *-3* |
| 1. Inform patients of negative consequences of sex without a condom | 0 | 1 | *-3* |
| 1. Assess patients for alcohol use | 0 | 1 | *-3* |
| 1. Counsel on alcohol reduction (if applicable) | 0 | 1 | *-3* |
| 1. Assess patient adherence to ARVs (if taking ARVs) | 0 | 1 | *-3* |
| 1. Assist patients with adherence to ARVs (if applicable) | 0 | 1 | *-3* |
| 1. Discuss getting ready to begin ART (if applicable) | 0 | 1 | *-3* |
| 1. Give patients condoms | 0 | 1 | *-3* |
| 1. Assist patients in developing a plan to change the behavior identified | 0 | 1 | *-3* |
| 1. Test partner(s) for HIV | 0 | 1 | *-3* |
| 1. Test couples for HIV | 0 | 1 | *-3* |

| 23. Write reasons why lay counselor did not discuss HIV prevention activities. |
| --- |

**Appendix O**

**Clinic Services Form**

| ***This section is completed every 6 months:*** |
| --- |

Instructions: Information on this form will be collected from clinic records or clinic databases in collaboration with the clinic administration or partners connected to clinic. This section should be completed every 6 months.

Clinic ID #**:** _________________

Data collector ID #**:** _________________

Source(s) of information**:** _________________

Date information was collected: ( _____ **/ _____ / ________** )

dd mm yyyy

Assessment Number:

_____ 1. Baseline

_____ 2. 6-month assessment

_____ 3. 12-month assessment

1. How many of each cadre is currently working at this HIV clinic? *[If there are no members of a certain cadre working at the clinic, enter “0” for that answer choice].*

_____1. Doctors

_____2. Clinical Officers

_____3. Nurse

_____4. Nurse assistants

_____5. Pharmacists

_____6. Counselors (not funded by the project)

_____7. Lay Counselors

2. Tick which days of the week this clinic is open and list the hours the HIV clinic is open.

| _____1. Monday  __________Time clinic opens  __________Time clinic closes  _____2. Tuesday  __________Time clinic opens  __________Time clinic closes  _____3. Wednesday  __________Time clinic opens  __________Time clinic closes  _____4. Thursday  __________Time clinic opens  __________Time clinic closes  _____5. Friday  __________Time clinic opens  __________Time clinic closes |
| --- |

3. How many total patients are there currently enrolled at the HIV clinic?

________ # total clinic patients

4. How many HIV-positive patients are currently attending the clinic for care and services but not taking antiretroviral medications?

________ # patients in care only

5. How many HIV-positive patients are currently on antiretroviral treatment?

________ # patients on ARVs

6. How many HIV-positive patients are seen at the clinic each day, on average?

________ # HIV-positive patients seen/day

7. How many HIV-positive patients on antiretroviral treatment have stopped coming to the clinic (defaulted) in the past 6 months?

________ # on ARVs – defaulted

8. How many HIV-positive patients currently attending the clinic for care and services but not taking antiretroviral medications have stopped coming to the clinic in the last 6 months?

________ # not on ARVs who stopped coming to the clinic

9. How many HIV-positive patients on antiretroviral treatment have missed appointments in the past 6 months?

________ # on ARVs missed appointments

10. How many HIV-positive patients currently attending the clinic for care and services but not taking antiretroviral medications have missed appointments in the last 6 months?

________ # not on ARVs who missed appointments

11. In this HIV clinic, how many HIV tests were conducted in the last 6 months?

________ # HIV tests

| ***The section below is completed monthly:*** |
| --- |

Clinic Name: _________________________________

Data collector ID #: _________________________________

Source(s) of information: _________________________________

Date this information was collected:

( _____ / _____ / __________)

dd mm yyyy

Data Collection Month: *[Tick one]*

_____ 1. January (1st – 31st)

_____ 2. February (1st – 28th)

_____ 3. March (1st – 31st)

_____ 4. April (1st – 30th)

_____ 5. May (1st – 31st)

_____ 6. June (1st – 30th)

_____ 7. July (1st – 31st)

_____ 8. August (1st – 31st)

_____ 9. September (1st – 30th)

_____10.October (1st – 31st)

_____11.November (1st – 30th)

_____12.December (1st – 31st)

1. Number of prescriptions or packets of contraceptive pills given to HIV-positive women enrolled at the HIV clinic in the past month.

**_____________** Number of Prescriptions

1. Number of prescriptions or packets of contraceptive injections given to HIV-positive women enrolled at the HIV clinic in the past month.

**_____________** Number of contraceptive injections

1. Number of HIV-positive patients in the HIV clinic treated for an STI in the past month.

**_____________** Number of patients

**Appendix P**

**Patient Medical Chart Review Form**

Instructions: Information on this form will be collected from patient’s clinic records including patient care forms completed by the health care providers and the Lay Counselor Record Form.

Clinic ID #**:** _____________

Data collector ID #: _____________

Patient ID #: _____________

Patient Gender: _____ Male

_____ Female

Patient Date of Birth: ( ____ **/ ____ / ______** ) (dd/mm/yyyy)

Date Form Completed: ( ____ **/ ____ / ______** ) (dd/mm/yyyy)

Assessment Number:

_____ 1. Baseline assessment

_____ 2. 6-month assessment

_____ 3. 12-month assessment

1. Date patient began receiving medical care for HIV (include care received at previous clinics if patient is a transfer from another clinic):

( ____ **/ ____ / ______** ) (dd/mm/yyyy)

2. Date diagnosed with HIV:

( ____ **/ ____ / ______** ) (dd/mm/yyyy)

3a. Date of last CD-4 count:

( ____ **/ ____ / ______** ) (dd/mm/yyyy)

3b. What was patient’s last CD-4 count?

_____ CD-4 count

4a. Most recent WHO Clinical Stage of HIV/AIDS:

_____ 1. Stage I

_____ 2. Stage II

_____ 3. Stage III

_____ 4. Stage IV

4b. Date of most recent WHO Clinical Stage?

( ____ **/ ____ / ______** ) (dd/mm/yyyy)

5. Is the patient currently taking HIV antiretroviral medications?

_____ 0. No

_____ 1. Yes

6. Date patient began ARVs

( ____ **/ ____ / ______** ) (dd/mm/yyyy)

7. For the last 6 months, list the patient’s prescribed HIV medications, dose, and number of days prescribed for each medication .

| **Date of visit /**  **date prescribed**  **(dd/mm/yyyy)** | **HIV Medication Name**  (include co-trimoxazole, if prescribed) | **Dose** | **# days prescribed** |
| --- | --- | --- | --- |
|  |  |  |  |
|  |  |  |  |
|  |  |  |  |
|  |  |  |  |
|  |  |  |  |
|  |  |  |  |
|  |  |  |  |
|  |  |  |  |
|  |  |  |  |

**8. Family Planning and Sexually Transmitted Infections over the last 6 months:**

| **Date of Clinic Appointment** | **Date:**  **___________**  (dd/mm/yyyy) | **Date:**  **___________**  (dd/mm/yyyy) | **Date:**  **___________**  (dd/mm/yyyy) | **Date:**  **___________**  (dd/mm/yyyy) | **Date:**  **___________**  (dd/mm/yyyy) | **Date:**  **___________**  (dd/mm/yyyy) | **Date:**  **___________**  (dd/mm/yyyy) | **Date:**  **___________**  (dd/mm/yyyy) | **Date:**  **___________**  (dd/mm/yyyy) |
| --- | --- | --- | --- | --- | --- | --- | --- | --- | --- |
| **Females Only** |  |  |  |  |  |  |  |  |  |
| Pregnant | __ 0. No  __ 1. Yes  __-1. Don’t know | __ 0. No  __ 1. Yes  __-1. Don’t know | __ 0. No  __ 1. Yes  __-1. Don’t know | __ 0. No  __ 1. Yes  __-1. Don’t know | __ 0. No  __ 1. Yes  __-1. Don’t know | __ 0. No  __ 1. Yes  __-1. Don’t know | __ 0. No  __ 1. Yes  __-1. Don’t know | __ 0. No  __ 1. Yes  __-1. Don’t know | __ 0. No  __ 1. Yes  __-1. Don’t know |
| **Pregnant women only:** | |  |  |  |  |  |  |  |  |
| Delivery date (dd/mm/yyyy) | ___________ | ___________ | ___________ | ___________ | ___________ | ___________ | ___________ | ___________ | ___________ |
| Taking Efavirenz | __ 0. No  __ 1. Yes | __ 0. No  __ 1. Yes | __ 0. No  __ 1. Yes | __ 0. No  __ 1. Yes | __ 0. No  __ 1. Yes | __ 0. No  __ 1. Yes | __ 0. No  __ 1. Yes | __ 0. No  __ 1. Yes | __ 0. No  __ 1. Yes |
| Referred to PMTCT | __ 0. No  __ 1. Yes | __ 0. No  __ 1. Yes | __ 0. No  __ 1. Yes | __ 0. No  __ 1. Yes | __ 0. No  __ 1. Yes | __ 0. No  __ 1. Yes | __ 0. No  __ 1. Yes | __ 0. No  __ 1. Yes | __ 0. No  __ 1. Yes |
| **Females and Males (spouse/partner)** | | |  |  |  |  |  |  |  |
| Family planning (FP) methods | __ 0. No  __ 1. Yes  **If yes:**  ⁮ 1. Pill  ⁮ 2. Injectables  ⁮ 3. Implants  ⁮ 4. Condoms  ⁮ 5. IUD  ⁮ 6. Other: ____________ | __ 0. No  __ 1. Yes  **If yes:**  ⁮ 1. Pill  ⁮ 2. Injectables  ⁮ 3. Implants  ⁮ 4. Condoms  ⁮ 5. IUD  ⁮ 6. Other: ____________ | __ 0. No  __ 1. Yes  **If yes:**  ⁮ 1. Pill  ⁮ 2. Injectables  ⁮ 3. Implants  ⁮ 4. Condoms  ⁮ 5. IUD  ⁮ 6. Other: ____________ | __ 0. No  __ 1. Yes  **If yes:**  ⁮ 1. Pill  ⁮ 2. Injectables  ⁮ 3. Implants  ⁮ 4. Condoms  ⁮ 5. IUD  ⁮ 6. Other: ____________ | __ 0. No  __ 1. Yes  **If yes:**  ⁮ 1. Pill  ⁮ 2. Injectables  ⁮ 3. Implants  ⁮ 4. Condoms  ⁮ 5. IUD  ⁮ 6. Other: ____________ | __ 0. No  __ 1. Yes  **If yes:**  ⁮ 1. Pill  ⁮ 2. Injectables  ⁮ 3. Implants  ⁮ 4. Condoms  ⁮ 5. IUD  ⁮ 6. Other: ____________ | __ 0. No  __ 1. Yes  **If yes:**  ⁮ 1. Pill  ⁮ 2. Injectables  ⁮ 3. Implants  ⁮ 4. Condoms  ⁮ 5. IUD  ⁮ 6. Other: ____________ | __ 0. No  __ 1. Yes  **If yes:**  ⁮ 1. Pill  ⁮ 2. Injectables  ⁮ 3. Implants  ⁮ 4. Condoms  ⁮ 5. IUD  ⁮ 6. Other: ____________ | __ 0. No  __ 1. Yes  **If yes:**  ⁮ 1. Pill  ⁮ 2. Injectables  ⁮ 3. Implants  ⁮ 4. Condoms  ⁮ 5. IUD  ⁮ 6. Other: ____________ |
| Who provided FP methods? | ⁮ 1. This clinic  ⁮ 2. FP clinic  ⁮ 3. Other clinic | ⁮ 1. This clinic  ⁮ 2. FP clinic  ⁮ 3. Other clinic | ⁮ 1. This clinic  ⁮ 2. FP clinic  ⁮ 3. Other clinic | ⁮ 1. This clinic  ⁮ 2. FP clinic  ⁮ 3. Other clinic | ⁮ 1. This clinic  ⁮ 2. FP clinic  ⁮ 3. Other clinic | ⁮ 1. This clinic  ⁮ 2. FP clinic  ⁮ 3. Other clinic | ⁮ 1. This clinic  ⁮ 2. FP clinic  ⁮ 3. Other clinic | ⁮ 1. This clinic  ⁮ 2. FP clinic  ⁮ 3. Other clinic | ⁮ 1. This clinic  ⁮ 2. FP clinic  ⁮ 3. Other clinic |
| Discussed safer pregnancy | __ 0. No  __ 1. Yes | __ 0. No  __ 1. Yes | __ 0. No  __ 1. Yes | __ 0. No  __ 1. Yes | __ 0. No  __ 1. Yes | __ 0. No  __ 1. Yes | __ 0. No  __ 1. Yes | __ 0. No  __ 1. Yes | __ 0. No  __ 1. Yes |
| **Females and Males: STI Syndromes** | | |  |  |  |  |  |  |  |
| STI Syndrome Identified | __ 0. No  __ 1. Yes | __ 0. No  __ 1. Yes | __ 0. No  __ 1. Yes | __ 0. No  __ 1. Yes | __ 0. No  __ 1. Yes | __ 0. No  __ 1. Yes | __ 0. No  __ 1. Yes | __ 0. No  __ 1. Yes | __ 0. No  __ 1. Yes |
| **If yes, write which STI(s) on the line to the right:**   - Vaginal discharge (VDS) - Urethral discharge (UDS) - Genital ulcer (GUD) - Pelvic inflammatory disease (PID) - Candidiasis - Bacterial vaginosis | **_____________**  List Syndrome(s) Identified  __ Treated at clinic  __ Referred for treatment  __ Partner treated | **_____________**  List Syndrome(s) Identified  __ Treated at clinic  __ Referred for treatment  __ Partner treated | **_____________**  List Syndrome(s) Identified  __ Treated at clinic  __ Referred for treatment  __ Partner treated | **_____________**  List Syndrome(s) Identified  __ Treated at clinic  __ Referred for treatment  __ Partner treated | **_____________**  List Syndrome(s) Identified  __ Treated at clinic  __ Referred for treatment  __ Partner treated | **_____________**  List Syndrome(s) Identified  __ Treated at clinic  __ Referred for treatment  __ Partner treated | **_____________**  List Syndrome(s) Identified  __ Treated at clinic  __ Referred for treatment  __ Partner treated | **_____________**  List Syndrome(s) Identified  __ Treated at clinic  __ Referred for treatment  __ Partner treated | **_____________**  List Syndrome(s) Identified  __ Treated at clinic  __ Referred for treatment  __ Partner treated |

9. Date of appointments, past 6 months:

| (dd/mm/yyyy) | (dd/mm/yyyy) | (dd/mm/yyyy) | (dd/mm/yyyy) | (dd/mm/yyyy) | (dd/mm/yyyy) |
| --- | --- | --- | --- | --- | --- |
|  |  |  |  |  |  |

| (dd/mm/yyyy) | (dd/mm/yyyy) | (dd/mm/yyyy) | (dd/mm/yyyy) | (dd/mm/yyyy) | (dd/mm/yyyy) |
| --- | --- | --- | --- | --- | --- |
|  |  |  |  |  |  |

10. List the dates HIV medications were dispensed and which medications were picked up during the last 6 months (from pharmacy records, if available).

| **Date ARV medications dispensed**  **(dd/mm/yyyy)** | **Names of ARV medications dispensed** | **# of days dispensed** | **Dose** |
| --- | --- | --- | --- |
|  |  |  |  |
|  |  |  |  |
|  |  |  |  |
|  |  |  |  |
|  |  |  |  |
|  |  |  |  |
|  |  |  |  |
|  |  |  |  |
|  |  |  |  |
|  |  |  |  |

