**Study timeline**

The following describes the project timeline after IRB approvals are obtained.

- October 2008: Pilot and revise questionnaires
- January – February 2009: Project enrollment and baseline
- February – March 2009: Intervention training for health care providers and lay counselors
- September – October 2009: 6-month Follow-up
- April – May 2010: 12-month Follow-up
- May – July 2010: Data cleaning and data analysis
- July 2010: Project results available

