***Medical Chart Review and Clinic Records Review***

Clinic Services: Integrating HIV prevention services into the HIV care and treatment clinic may impact overall clinic services and numbers of patients seen. The Clinic Services Form (Appendix O) will capture HIV services at the clinic level over time. Specifically, the number of patients enrolled at the clinic in care and on treatment, number of patients seen daily and weekly, number of patients who defaulted or were lost to follow-up, number of contraceptives provided to HIV-positive women prescribed through the HIV care and treatment setting, the number of treatment packages for STI syndromes dispensed to HIV-positive patients prescribed through the HIV care and treatment clinics, and number of HIV tests conducted will be recorded over the project period. The project staff will complete this form for intervention and comparison clinics by checking clinic records and log books.

Medical Chart Review: The Patient Medical Chart Review Form will record information from the medical charts of enrolled participants (Appendix P). Information recorded will include dates of HIV clinic visits for the year prior to enrollment, clinical indicators of HIV (e.g., CD4 count, WHO classification), medications, partner’s HIV status, reproductive health history, STI symptoms syndromically identified and STI treatment provided. Other information available in the medical chart will be recorded such as provider-delivered prevention messages, family planning, and STI management. These data will be collected for the year prior and during the year of the project. Information from the lay counselor record form maintained in the patient chart will also be extracted including number of visits, length of visits, and topics discussed. The project staff will complete this form for intervention and comparison clinics.

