Clinic Services: The Clinic Services Form (Appendix O) captures HIV care and services delivered as well as contraceptives and STI treatment medications dispensed to HIV-positive patients at the clinic level. This will be completed by the project coordinator monthly in all clinics. The project coordinator will gather this clinic-level information from clinic records and clinic administrators.

Medical Chart Review: After each participant’s follow-up visit the study interviewer or coordinator will use the patient’s medical chart to gather information such as the clinic visits since last extraction, clinical indicators of HIV (e.g., CD4 count, WHO classification), medications, partner’s HIV status, reproductive health history, STI treatment provided (see Appendix P).

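### Appendix P items 7–10 look back 6 months, against text that promises the prior year and the whole interval between extractions; following the form leaves about 3 of 15 months unrecorded on those items

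*Protocol*

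**What the plan says.** Three places in the protocol define the period that chart abstraction covers, and they differ.

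- **Study instruments, Medical Chart Review.** Clinic visit dates are to be recorded for the year before enrolment. After listing further chart content, the paragraph ends: "These data will be collected for the year prior and during the year of the project".
- **Data collection, Medical Chart Review.** After each follow-up visit, staff use the chart to "gather information such as the clinic visits since last extraction", along with medications, reproductive history and STI treatment.
- **Appendix P, the form itself.** Item 7: "For the last 6 months, list the patient’s prescribed HIV medications, dose, and number of days prescribed for each medication". Item 8: "Family Planning and Sexually Transmitted Infections over the last 6 months". Item 9: "Date of appointments, past 6 months". Item 10: "List the dates HIV medications were dispensed and which medications were picked up during the last 6 months".

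Table 2 has the form completed three times: at baseline, 6 months and 12 months. The Study timeline gives "January – February 2009: Project enrollment and baseline" and "September – October 2009: 6-month Follow-up", with the 12-month follow-up in April–May 2010. The first interval exceeds 6 months on purpose: Data collection times the 6-month visit from the point at which the intervention is in place in the clinics, not from each participant's baseline.

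**The concern.** A 6-month look-back covers the whole interval only if extractions are at most 6 months apart, and on the protocol's own calendar they are further apart than that. Nothing in the protocol tells the abstractor to go beyond the 6 months printed on items 7 to 10. If the form is followed, a stretch after baseline and another after the first follow-up go unrecorded on those items, and half of the promised pre-enrolment year is missing.

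The items feed listed outcomes: ARV adherence (dispensing), STIs, pregnancy, and family planning services. No other participant-level source fills the gap. The patient questionnaire asks about clinic visits, discharge and sores over the past 6 months and about pregnancy at the time of interview, while the monthly part of the Clinic Services Form holds clinic totals. Late repair is also limited. Data entry, editing, and management has the link between names and study numbers destroyed within three months of the end of 12-month data collection, after which the charts can no longer be matched to participants.

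**Working it through.** **Inputs.** Study timeline windows: baseline 1 Jan–28 Feb 2009, first follow-up 1 Sep–31 Oct 2009, second follow-up 1 Apr–31 May 2010. Look-back on items 7–10: 6 months. One month = 30.4375 days. The protocol states no coverage figure to reproduce.

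**Formula.** Unrecorded time = max(0, interval 1 − 6) + max(0, interval 2 − 6).

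| Dates used | Interval 1 | Interval 2 | Total | Unrecorded |
|---|---|---|---|---|
| Window midpoints (30 Jan 2009, 1 Oct 2009, 1 May 2010) | 244 d = 8.02 | 212 d = 6.97 | 14.98 | 2.02 + 0.97 = 2.98 |
| Window starts | 7.98 | 6.97 | 14.95 | 2.95 |
| Window ends | 8.05 | 6.97 | 15.01 | 3.01 |

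Each way, about 3 of 15 months, or 20%, is unrecorded. At the midpoints the two stretches run from about 30 January to 1 April 2009 and from about 1 to 31 October 2009.

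**Spread between participants.** Interval 1 can run from 6.1 to 10.0 months and interval 2 from 5.0 to 8.9. If each date is uniform and independent within its window (an assumption), the mean unrecorded time is 3.0 months, with a 95% range of 1.6 to 4.5. Nobody escapes: the shortest possible total is 13.0 months and two look-backs cover at most 12, so at least about 1 month is unrecorded for everyone.

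**Time after implementation.** The timeline puts training in February–March 2009 but gives no implementation date, so two are assumed.

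| Assumed start | Mean unrecorded time after start | Mean follow-up after start | Share |
|---|---|---|---|
| 1 April 2009 | 1.3 months | 13.0 months | 1.28 / 12.99 = 10% |
| 1 March 2009 | 2.1 months | 14.0 months | 2.06 / 14.01 = 15% |

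**Before enrolment.** Promised 12 months, form 6 months: 12 − 6 = 6 months unrecorded.

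**If items 7–10 ran from the previous extraction.** Unrecorded time between baseline and the last extraction falls from about 3.0 months to 0.

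**The case against.** The strongest reply is that the Data collection instruction already covers the whole interval, so staff may follow it and lose nothing. The form has some room for that: item 8 has 9 visit columns and item 9 has 12 date boxes, and even monthly attendance over 8 months gives about 8 visits. This stands to the extent that the loss is conditional on the form being followed. It does not remove the contradiction. The instruction attaches the longer period to clinic visits without amending the printed limits, and a baseline year of monthly visits (12) would not fit 9 columns.

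Several limits on the consequences also stand.

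- Items 1 to 6 (including CD4 count, WHO stage, ARV status and start date) and the lay counselor record carry no 6-month limit. A reader might infer that all chart data are cut short; the form does not support that.
- A reader might infer that 20% of intervention exposure goes unobserved. Most of the first gap coincides with training, and the first follow-up is timed so that 6 months reaches back roughly to implementation.
- A reader might infer bias between arms. Follow-up interviews take place in the same period in both, so the design builds in no imbalance.
- The monthly clinic totals continue without a gap and serve the service-delivery hypothesis at clinic level. Many pregnancies that begin in a gap will still show at later visits, so discrete events suffer most.
- The protocol does not say that visit counts for the intervention-received analysis come from Appendix P, so harm to that analysis is possible but not shown.

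**Conclusion.** The point holds as an inconsistency between form and text that affects which data exist. If the abstractor follows Appendix P, items 7 to 10 miss about 3 of 15 months: about 2 after baseline, largely in the February–March 2009 training window, and about 1 after the first follow-up. Roughly 1 to 2 of those months fall after implementation, depending on its assumed start. A further 6 of 12 pre-enrolment months are missed. These figures rest on the planned calendar and on the printed limits being applied literally.

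The documents do not support saying that the data are certain to be lost, since the text instructs otherwise. The primary outcome used for sample size, self-reported unprotected sex in the past 3 months, is untouched. What is at risk is participant-level information on visits, refills, STI episodes and contraception. It is worth correcting before abstraction starts, because analysis cannot recover what was not abstracted.

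**What to change.** Reconcile the two Medical Chart Review paragraphs with Appendix P by giving items 7 to 10 one look-back: *since the last chart extraction (at baseline: the 12 months before enrolment)*. Provide enough rows and columns for the longest period, including 12 months of visits at baseline. Add the start date of the period abstracted; the form already carries its completion date. How to allow for unequal observation time, for example by rates per person-month, is an optional analysis choice and need not be settled on the form.

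The cost is a wording and layout change and slightly longer abstraction at each extraction. No new visits are needed.
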